#### 2.9.2. Multivariate Data Analysis

For the NMR metabolomics analyses in feces, multivariate modeling will be performed in MATLAB (Mathworks Inc., Natick, MA, USA), using in-house scripts as previously described [57]. Briefly, it will firstly include a principal component analysis (PCA) to identify clusters and outliers, followed by pairwise comparisons between dietary groups using an orthogonal projection to latent structures discriminant analysis (OPLS-DA) to identify discriminatory metabolites. Colors projected onto an OPLS coefficient plot will indicate the correlation coefficient (r2) between each metabolite and grouping variable, with red indicating strong significance and blue indicating weak significance.

For the metabolomics and metagenomics data, unsupervised hierarchical clustering analysis (HCA) will be performed to identify general patterns of gut-derived metabolites or gut microbiota variations between samples, based on metabolites identified in the OPLS-DA models or bacterial genera present in at least the 5% of the samples and with ≥1% abundance. Data will be standardized as z-scores across samples for each metabolite and microbial genera before clustering so that the mean will be 0 and the SD will be 1.

For clustering identification, a multivariate approach based on PCA, partial least squares discriminant analysis (PLS-DA) and HCA, including the anthropometric and biochemical parameters, food intake biomarkers and phenolic metabolites, gut-derived metabolites, and bacterial genus abundances will be carried out after data normalization and autoscaling.

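### The metabolite clustering described as unsupervised uses only metabolites chosen with the diet labels, so it leans toward diet separation and cannot independently support a diet effect

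*Protocol article*

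**What the plan says.** Protocol article, Section 2.9.2, sets out the fecal NMR metabolomics analysis in this order:

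- A PCA, which does not use the diet label, looks for clusters and outliers.
- It is "followed by pairwise comparisons between dietary groups using an orthogonal projection to latent structures discriminant analysis (OPLS-DA) to identify discriminatory metabolites".
- In the next step, applied to both omics data types, "unsupervised hierarchical clustering analysis (HCA) will be performed to identify general patterns of gut-derived metabolites or gut microbiota variations between samples".
- For metabolites, the input to that step is given as "variations between samples, based on metabolites identified in the OPLS-DA models". For genera, it is a filter on prevalence (5% of samples) and on abundance of at least 1%.
- "Data will be standardized as z-scores across samples for each metabolite and microbial genera before clustering".

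The legend of the OPLS coefficient plot shows r2 between each metabolite and the grouping variable as colours, "with red indicating strong significance and blue indicating weak significance".

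A separate HCA on the combined clinical, biomarker and omics variables is planned later in the section, with no OPLS-DA preselection stated. The details of the OPLS-DA modelling are left to in-house scripts described in a cited source.

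**The concern.** The clustering algorithm takes no labels, but its metabolite input has already been chosen with them. OPLS-DA keeps the metabolites that differ most between the Mediterranean and low-fat arms in this sample, whether the difference is real or due to chance. Clustering the same samples on those metabolites partly repeats the selection. It also defeats the stated aim of finding general patterns, because metabolites that vary for reasons other than diet are removed first.

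The two halves of one analysis follow different rules. Genera are filtered without labels and metabolites with them, so the metabolite heat map may look more diet-separated than the genus heat map for that reason alone.

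What is at stake is interpretation. The Discussion presents the omics work as a main novelty and strength and as a route to mechanism. A reader who sees diets separate in a clustering described as unsupervised may take it as support for the OPLS-DA result, when it is not independent of it. The BMI z-score primary outcome is not touched.

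**Working it through.** The article gives no figure to reproduce here, so the check is a simulation in which the two diets are identical.

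**Inputs from the article.** 120 per arm (Section 2.1) and 20% dropout (Section 2.8): 120 × (1 − 0.20) = 96 per arm, 192 samples. Features are z-scored before clustering (Section 2.9.2).

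**Assumptions, not in the article.**
- Number of metabolites: 20, 50, 200 or 1000, either independent or correlated through 10 common factors.
- OPLS-DA with one predictive and one orthogonal component.
- Selection by VIP>1, by correlation with diet at p<0.05, or (200 features only) the 20 largest weights.
- One sample per participant; Ward linkage unless stated; tree cut at two clusters; 150 runs per setting.

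**Measures.** (a) Share of runs with Fisher exact p<0.05 for cluster against diet. (b) Agreement = max(a, 1 − a), where a is the fraction of samples whose cluster matches their diet. Because the better matching is taken, chance agreement is a little above 50%.

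**Results, 96 per arm, Ward linkage, no diet effect:**

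| Metabolites | Association, OPLS-DA-selected | Association, all features | Agreement, selected |
|---|---|---|---|
| 20 | 13–33% | 4–9% | 54–56% |
| 50 | 17–53% | 1–6% | 54–57% |
| 200 | 42–74% | 1–5% | 56–59% |
| 1000 | 62–99% | 3–6% | 58–68% |

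Agreement with all features was 52–53%. The Monte Carlo standard error of a true 5% rate over 150 runs is √(0.05 × 0.95 / 150) = 1.8 percentage points, so 1–9% is about the nominal level.

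**Sensitivity.**
- *Linkage* (200 features, VIP>1): average linkage gave 0–1% association and 51% agreement; complete linkage gave 15% and 53%.
- *Sample size*: at 40 per arm with Ward linkage, 200 features and VIP>1 gave 53–63% association and 62–65% agreement. With 1000 independent features and p<0.05 selection the figures were 100% and 85%. All-feature clustering gave 1–6% association and 54% agreement.
- *Runs with nothing to cluster*: under p<0.05 selection, only 43–44 of 150 runs with 20 features, and 103 of 150 with 50, selected at least two metabolites. About 71% and 31% of those null runs could not be clustered at all. Percentages for these settings refer to evaluable runs.
- *Simpler rule*: a second simulation (200 datasets per setting, Ward linkage, independent features) always kept a fixed number of metabolites with the largest absolute covariance with diet. Association was 36.5% (5 of 50), 39% (10 of 100), 55.5% (10 of 200) and 55.5% (20 of 200), against 3–5.5% with all features.

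**The r2 legend.** With 192 samples, two-sided p = 0.05 corresponds to t ≈ 1.97 on 190 degrees of freedom, so r2 = t²/(t² + 190) = 3.88/193.88 ≈ 0.02. A metabolite shown at the weak end of the scale can still be nominally significant.

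**The case against.** The strongest case on the other side has five parts.

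1. *The effect is not inevitable.* A reader might infer that the clustering will show diet groups even when the diets do not differ. The simulations do not support that. In many settings a large share of null runs shows no association, average linkage removes the effect at 200 features with VIP>1, and agreement of 54–59% with 20–200 features would hardly be visible on a heat map. This stands.
2. *The size rests on choices the article does not make.* It states no metabolite count, selection threshold, linkage or cut, and plans no test of cluster against diet. This stands, and is why only a range is given.
3. *Validation may exist elsewhere.* A reader might infer that the OPLS-DA models go unvalidated. The article defers the modelling to a cited method, so silence on cross-validation or permutation is not an error. If failed models are dropped, a null model would usually pass nothing on to the clustering. But where a model does pass, its metabolites are still label-selected, so such a gate does not make the clustering unsupervised in substance.
4. *No claim of confirmation is made.* The stated aim is general patterns, a label-blind PCA comes first, the integration in Section 2.9.3 is openly supervised, and the Conclusions call for larger cohorts to validate the biomarkers. A reader might infer that the plan offers this HCA as proof of a diet effect; it does not say so. The mismatch between the description, the aim and the input remains.
5. *The colour legend is harmless.* At a fixed sample size r2 and the univariate p-value rank metabolites identically. This stands as far as ranking goes, so the legend is only a wording point.

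**Conclusion.** The point holds in a limited form. For metabolites, the HCA in Section 2.9.2 is not unsupervised in substance: the diet label chooses the features. It is biased toward diet separation and cannot serve as independent evidence of a diet effect. This follows from the stated rule, not from missing detail, and the label-free genus filter in the same sentence shows the alternative.

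The size of the bias is uncertain. At 96 per arm with Ward linkage and two clusters, a spurious nominal association arose in about 13–99% of evaluable null runs against 1–9% without label selection, but in 0–1% with average linkage (200 features, VIP>1). Agreement with diet was about 51–68% across the linkages tried. These figures rest on an assumed 20 to 1000 metabolites, the assumed selection rules, and no validation gate before selection. They do not show that diet clusters will appear when there is no effect.

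The genus clustering is not affected, and the later HCA on combined variables states no OPLS-DA preselection. This is a secondary, exploratory analysis.

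**What to change.** Run the metabolite HCA on all quantified gut-derived metabolites, or on a set filtered by a rule that ignores diet, as is already done for genera. If a heat map of OPLS-DA-selected metabolites is also wanted, label it a descriptive display of supervised selection and do not call it an unsupervised result. As a minor wording change, describe the r2 colours as strength of correlation and not as significance.

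The cost is a change of text and one rerun of the clustering, with no new data. The heat map may look less clean.

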#### 2.9.3. Data Integration: Systems Biology Approach

The systems biology approach aims to integrate the multiple layers of information generated in the course of the study (classical anthropometric and biochemical biomarkers of health, AGEs, dietary and physical habits, social aspects, food intake biomarkers and omics data (gut microbiota and gut-derived metabolites) to extract conclusions from a holistic point of view. The system biology approach will allow gaining a detailed understanding of the mechanisms by which the MD intervention exert its effects and to identify a combination of biomarkers that accurately characterizes the changes induced by the MD intervention. The integration of the anthropometric and biochemical data, metagenomics, and metabolomics will be based on mixDIABLO (http://mixomics.org/mixdiablo/ (accessed on 20 December 2020)), which is an integrative method to identify multi-omics biomarker panels that can discriminate between multiple phenotypic groups. DIABLO uses PLS and extends both sparse PLS-DA to multi-omics analyses and sparse Generalized Canonical Correlation Analysis to a supervised analysis framework [58].

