(2)The low-fat diet (control diet) consists of a restricted consumption of fats. This diet will be based on the one proposed as low-fat diet in the PREDIMED study [45], and it will provide 55% of energy from carbohydrate, 25–30% from fat, and 15–20% from protein. The low-fat diet is the most used diet for obesity treatment in adolescents [42]. This group will not receive any additional specific food by the researchers.

Volunteer’s compliance with the dietary prescription will be assessed by means of self-reported weekly food checklists, 3-day dietary records, and selected biomarkers of food intake.

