## 3. Discussion

The identification of lifestyle factors, including adoption of dietary patterns, to counteract the troubling youth obesity epidemic, is of primary importance. However, it is still unclear which strategies or combination of strategies are effective in different contexts across the globe for obesity prevention in young people. In this framework, the MED4Youth project will develop, for the first time, a multicenter nutritional intervention study to evaluate the health benefits of the MD against youth obesity and associated CVD risk factors.

The novelty of the MED4Youth project relies on, firstly, carrying out a multicenter clinical and nutritional intervention study for 4 months, including ICT educational tools, specifically targeting 240 obese adolescents (13–17 years) from different Mediterranean countries (Spain, Portugal, and Italy), and, secondly, the application of omics technologies and a systems biology approach to elucidate whether the MD could shape the gut microbiota and gut-derived metabolites, trying to pinpoint the mechanisms by which MD exert its beneficial effects against youth obesity and CVD risk factors.

Moreover, the MED4Youth project will contribute to valorizing Mediterranean products, especially foods not widely consumed in European Mediterranean developed countries (sourdough bread, hummus, and pomegranate), promoting their consumption in the overall population, especially in adolescents, and paving the way for a high, long-term demand of these products, fostering the competitiveness of processing industries and reinforcing local production systems.

Another strong point of this intervention study is that subjective, conventional dietary assessment tools will be combined with targeted metabolomics analyses of selected food intake biomarkers to provide a more accurate fingerprinting of individuals’ dietary pattern. This will allow establishing robust associations between MD adherence and health status. In addition, the analysis of the inter-individual differences associated with particular biomarkers of intake of some plant products and phenolic classes will serve to assess the true internal exposure to certain bioactive compounds. This personalized approach will represent a step forward toward improving dietary exposure evaluation, allowing a more objective and robust assessment of the dietary pattern of the adolescent.

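### Food-intake markers sit in the same PLS-DA as health and gut variables, and possibly in DIABLO, so a diet-discriminating panel can separate the arms without any biological response

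*Protocol article*

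**What the plan says.** **Section 2.9.2 (Multivariate Data Analysis).** The last paragraph describes a combined PCA, PLS-DA and HCA, "including the anthropometric and biochemical parameters, food intake biomarkers and phenolic metabolites, gut-derived metabolites, and bacterial genus abundances". Entry of the intake markers into a supervised model is explicit here. The stated purpose is to identify clusters, and the PLS-DA class label is not given.

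**Section 2.9.3 (Systems Biology Approach).** The layers of information to be integrated include "dietary and physical habits, social aspects, food intake biomarkers and omics data". The sentence on method is narrower: "The integration of the anthropometric and biochemical data, metagenomics, and metabolomics will be based on mixDIABLO". DIABLO is presented there as a supervised way to find panels that discriminate between groups. The section expects insight into how the MD works, and a panel "to identify a combination of biomarkers that accurately characterizes the changes induced by the MD intervention".

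**Status of the intake markers.** The Discussion speaks of "targeted metabolomics analyses of selected food intake biomarkers", and Table 2 also gives targeted metabolomics as their tool (urine, V1 and V3). Section 2.3 uses selected intake biomarkers to assess compliance. The Discussion calls them an objective measure of adherence and links them to internal exposure to bioactive compounds.

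**What each arm is given.** Sections 2.3 and 2.6 supply the MD arm with sourdough bread, pomegranate juice, chickpeas/hummus, mixed nuts and extra virgin olive oil, and describe the MD as rich in phenolic compounds. Of the control arm, section 2.3 says: "This group will not receive any additional specific food by the researchers".

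**The concern.** The article gives the intake markers two roles. In section 2.3 they show whether the prescribed food was eaten. In section 2.9.2 they are predictors next to the variables that are supposed to respond to that food. A supervised model rewards whatever separates the classes. If the classes are the diet arms, a marker of a food handed to one arm only can separate them because the food was eaten, whatever happened to metabolism or microbiota.

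What is at stake is the trial's mechanistic aim: whether the MD shapes the gut microbiota and gut-derived metabolites, and by what route. A panel with high discrimination could be reported as characterizing the MD's effects when most of its discrimination comes from the exposure itself. Cross-validation offers no protection, since the markers really do differ between arms and the difference recurs in held-out data.

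**Working it through.** **Where the markers enter.**
- PLS-DA in 2.9.2: explicit, since intake biomarkers and phenolic metabolites are named among the variables.
- DIABLO in 2.9.3: possible, not stated. The method sentence names anthropometric and biochemical data, metagenomics and metabolomics. The intake markers come in only if metabolomics covers them, as the Discussion and Table 2 suggest.
- Dietary habits: named as a layer to integrate, but not placed in any supervised model.

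**Sample size for the illustration.** The plan's total follows from section 2.8: difference 0.2, SD 0.5, two-sided α 0.05, power 80%.

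n per arm = 2 × [0.5 × (1.960 + 0.842) / 0.2]² = 98.1, rounded up to 99.

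For 20% dropout, 2 × 98.1 / 0.8 = 245, and multiplying 99 by 1.2 gives 119 per arm, 238 in all. The stated 240 lies between these. With 120 per arm and 20% lost, 120 × 0.8 = 96 per arm are analysed. The point does not otherwise depend on this figure.

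**Simulation.** The article gives no number of markers, correlation or between-arm shift, so all three are assumptions. Every health and gut variable is pure noise with no arm effect. Each intake marker is shifted by d SD in the MD arm. The classifier is a two-component PLS-DA on one pooled set of variables, scored by cross-validated AUC:

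AUC = [R₁ − n₁(n₁ + 1)/2] / (n₁n₀), where R₁ is the rank sum of the predicted scores in the MD arm.

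- Setting A: 60 null variables, 4 markers, 5-fold cross-validation, 200 replicates.
- Setting B: 120 null variables, 3, 5 or 10 markers with pairwise correlation 0.3, 7-fold cross-validation, 60 replicates. Ranges are over the number of markers.

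| Shift d (SD) | A, markers in | B, markers in | Markers out (A; B) |
|---|---|---|---|
| 0.3 | not run | 0.53 | –; 0.49–0.50 |
| 0.5 | 0.65 | 0.58–0.59 | 0.50; 0.49–0.51 |
| 1.0 | 0.85 | 0.72–0.79 | 0.50; 0.49–0.51 |
| 1.5 | 0.96 | 0.84–0.91 | 0.51; 0.50–0.52 |
| 2.0 | 0.99 | 0.93–0.97 | 0.50; 0.49–0.50 |

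In setting B, from d = 0.8 upward practically every intake marker was among the ten highest-weighted variables.

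**Closed-form check of setting B.** With m markers at correlation ρ = 0.3, the best linear score from the markers alone has

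AUC = Φ(√{m d² / [2(1 + (m − 1)ρ)]}).

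- d = 1: m = 3 gives Φ(√(3/3.2)) = 0.83; m = 10 gives Φ(√(10/7.4)) = 0.88.
- d = 2: m = 3 gives Φ(√(12/3.2)) = 0.97; m = 10 gives Φ(√(40/7.4)) = 0.99.

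The simulated values lie below these ceilings, as expected when 120 noise variables dilute the score. The separation therefore comes from the markers and is not overfitting.

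**The case against.** Several points on the other side stand and limit the claim.

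- **DIABLO.** Its sentence does not name intake markers. The sentence before it lists them apart from the omics data, which it describes as gut microbiota and gut-derived metabolites. A reader might infer that intake markers and dietary habits are certainly DIABLO predictors; the text does not say so. DIABLO also selects within blocks, and the simulation used one pooled, non-sparse block. It therefore does not show that intake markers would rank first or crowd out gut variables in DIABLO.
- **Class label.** It is not spelled out for the PLS-DA in 2.9.2, and the mechanistic wording stands in 2.9.3. Diet arm is the natural reading given the aim, but it is a reading.
- **Which foods the markers track.** The article does not list them, and controls are not barred from nuts, legumes or olive oil. A large shift is plausible from the supplied foods and the phenolic content of the MD, but its size is unknown.
- **Other analyses.** Health and gut effects are also tested without these markers: ANCOVA for anthropometric and biochemical variables, Mann–Whitney tests with Benjamini–Hochberg adjustment for bacteria, and fecal NMR OPLS-DA. The mechanistic question does not rest on this panel alone.
- **Purpose.** Relating exposure to health status is a stated aim in the Discussion, and altered phenolic metabolites are in a sense changes caused by the diet. Removing the intake markers from every analysis would go too far.

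It can also be said that block composition is detail for a fuller plan. That does not answer section 2.9.2, which states the pooled list outright. Nor does any of these points make a panel containing exposure markers evidence of biological response.

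**Conclusion.** The concern holds in a limited form. The PLS-DA in 2.9.2 mixes exposure markers with response variables, and DIABLO in 2.9.3 may do so. If diet arm is the class, the resulting panel can discriminate well with no change in any health or gut variable.

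The size depends on the assumed shift: separation is strong at 1 SD or more, weak at 0.3–0.5 SD, and absent once the markers are removed. A reader might infer that the panel will separate the arms whatever happens. The documents do not support that, because it depends on adherence and marker sensitivity, on which they give no figures. A reader might also infer that the mechanistic aim fails altogether; the analyses that do not use intake markers rule that out. The primary BMI z-score comparison is untouched.

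What does not stand is reading such a panel, by itself, as mechanism or as response to the MD.

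**What to change.** In sections 2.9.2 and 2.9.3:

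1. State the class label of the PLS-DA and DIABLO models and the variables in each block.
2. State that the MD response panel used for mechanistic conclusions is built from the anthropometric, biochemical, gut-metabolite and microbiota variables only, and report its cross-validated performance on those variables.
3. Keep food-intake biomarkers and phenolic metabolites as a separate exposure block, used for compliance and related to the response panel. This preserves the association aim in the Discussion.
4. Report any all-variable model alongside, labelled as including exposure.

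This needs no new data. It costs a change of wording and a little more analysis, and the reported discrimination will probably be lower.

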## 3. Discussion

The identification of lifestyle factors, including adoption of dietary patterns, to counteract the troubling youth obesity epidemic, is of primary importance. However, it is still unclear which strategies or combination of strategies are effective in different contexts across the globe for obesity prevention in young people. In this framework, the MED4Youth project will develop, for the first time, a multicenter nutritional intervention study to evaluate the health benefits of the MD against youth obesity and associated CVD risk factors.

The novelty of the MED4Youth project relies on, firstly, carrying out a multicenter clinical and nutritional intervention study for 4 months, including ICT educational tools, specifically targeting 240 obese adolescents (13–17 years) from different Mediterranean countries (Spain, Portugal, and Italy), and, secondly, the application of omics technologies and a systems biology approach to elucidate whether the MD could shape the gut microbiota and gut-derived metabolites, trying to pinpoint the mechanisms by which MD exert its beneficial effects against youth obesity and CVD risk factors.

Moreover, the MED4Youth project will contribute to valorizing Mediterranean products, especially foods not widely consumed in European Mediterranean developed countries (sourdough bread, hummus, and pomegranate), promoting their consumption in the overall population, especially in adolescents, and paving the way for a high, long-term demand of these products, fostering the competitiveness of processing industries and reinforcing local production systems.

Another strong point of this intervention study is that subjective, conventional dietary assessment tools will be combined with targeted metabolomics analyses of selected food intake biomarkers to provide a more accurate fingerprinting of individuals’ dietary pattern. This will allow establishing robust associations between MD adherence and health status. In addition, the analysis of the inter-individual differences associated with particular biomarkers of intake of some plant products and phenolic classes will serve to assess the true internal exposure to certain bioactive compounds. This personalized approach will represent a step forward toward improving dietary exposure evaluation, allowing a more objective and robust assessment of the dietary pattern of the adolescent.

On the other hand, the multidisciplinary consortium will allow exchanging best practices among Mediterranean basin countries regarding adherence to MD, creating a common knowledge and understanding on how MD can be effective toward preventing youth obesity, fostering long-lasting results and supporting policies to prevent and ameliorate obesity across the Mediterranean basin.

MD is characterized by a high palatability, the use of herbs and spices, and the election of traditional culinary techniques, and this will facilitate adherence to the intervention and will increase long-term compliance, in contrast to most of the low-calorie diets prescribed these days, which are less tasty and difficult to follow, especially in the long term. However, there is a low adherence to MD among the youth population of different Mediterranean countries, with around 10% of adolescents showing a medium–high adherence and 21% present a low adherence to this diet (low adherence 0–3 points/12; medium adherence 4–7 points/12; high adherence: 8–12 points/12) [20,21]. Therefore, there is a clear interest in identifying palatable healthy foods to try to increase the adherence to MD. Thus, in the present project, some traditional Mediterranean foods are proposed to the volunteers of all the centers, which are all characterized by a healthy nutrient profile and still very palatable, namely nuts, chickpeas/hummus, and sourdough bread. In particular, the bread will be made with flours from ancestral cereals and cereals with a lower gluten content, with a higher fiber content, and a lower carbohydrate content than conventional fast-fermenting bread made with white wheat. The inclusion of sourdough bread is based on previous scientific research that showed improved nutritional quality and beneficial effects on health with respect to the use of conventional breads, through the induction of satiety, a better control of the glycemic and insulinemic responses, the attenuation of systemic inflammation, and a favourable modulation of the gut microbiota [59,60,61,62]. Nuts, hummus/chickpeas, and pomegranate juice are rich sources of different bioactive compounds with putative cardioprotective effects that can contribute to reducing obesity, such as MUFA, PUFA, fiber, vitamins E and C, and different phenolic compounds [35,63,64,65]. There is strong evidence pointing towards a beneficial impact of nuts consumption on different cardiovascular risk factors, while their intake has been reported to help in the process of weight loss [66]. 

Moreover, different studies suggest that hummus and chickpeas may play a beneficial role in weight management and glucose control, as well as have a positive impact on some markers of CVD [38,63]. Finally, pomegranate and pomegranate juice are a rich source of polyphenolic compounds, which have shown several beneficial effects on human health [67], could positively impact the gut microbiota, and have been shown to contribute the modulation of metabolic disorders, including insulin resistance, which is typically associated to obesity [35,36,37]. Pomegranate juice intake has also been related with improvements on endothelial function in adolescents [68]. In the MED4Youth project, pomegranate will be consumed as pomegranate juice (delivered in frozen form) in order to facilitate and ensure its intake in the volunteers.

Some psychologists emphasize the importance of creating new habits, changing people in their daily context, influencing their habits and their basic psychology, rather than following traditional approaches based on simply providing information and education, to achieve a sustained change in behavior that has a beneficial impact on health [69,70]. Related with this issue, the MED4Youth project targets adolescence (13–17 y) as a key and sensitive development stage of life, where healthy lifestyles and behavioral flexibility need to be reinforced. For this reason, obese adolescents will be provided with an educational web-application where they can learn about health, nutrition, and food in general. Moreover, the motivational interview, using a nonjudgmental, empathetic, and encouraging tone, has shown to favor behavior change in adolescents, including the adoption of healthy dietary habits [44,53]. For this reason, the motivational interview used in the MED4Youth project will be focused on behavioral change, motivation for change, and no confronting.

Some potential limitations need to be taken into account. First, while volunteers in the MD group will receive some foods to be included in their diet, volunteers in the control group will not, so adherence to the low-fat control diet may be lower. Second, due to the nature of the interventions, participants and dietitians/nutritionists cannot be blinded, although researchers who will perform all biochemical and -omics determinations as well as statistical analyses will be. Another limitation is the short follow-up period (4 months) that might limit conclusions on the long-term effects. On the other hand, the major strengths of the study can be listed: (a) this is the first large RCT to evaluate the health benefits of the MD against youth obesity and associated CVD risk factors, with a total of 240 volunteers; (b) this is a multicentric study carried out in three different Mediterranean countries, which facilitates the generalization of the conclusions achieved from this study; (c) adherence in both groups will be fostered through the availability of an educational web-application intended to be used by both parents and adolescents, which provides information related to health and nutrition as well as recipes, and that will allow a “learning-through-playing” approach; (d) the use of food intake biomarkers provides an objective assessment of adherence to dietary interventions and a robust measurement of the dietary pattern of the volunteers; and (e) the application of omics technologies and a systems biology approach, together with the wide range of biomarkers analyzed, will provide a significant progress in the current knowledge on the mechanisms implicated in the beneficial effects of MD as well as the role of gut microbiota in these effects.

